### Data analysis

The quantitative analysis of effectiveness will be based on intention-to-treat with pairwise comparisons of the three arms. Descriptive statistics such as the mean, standard deviation, median, and range will be presented for continuous variables. The intervention effects on outcomes will be assessed using mean differences for continuous outcomes and risk ratios (RRs) and absolute risk differences for binary variables. Data will be analysed using STATA/SE version 15 (StataCorp LLC, College Station, TX).

Efforts will be made to minimize missing data. Primary analyses will be based on complete case analysis. To evaluate the robustness of our findings, we will perform sensitivity analysis using inverse probability weighting.

For analysis of secondary outcomes at 7 and 18 weeks, participants in the SAATHI-I and SAATHI-IG arms will be combined and considered as a single intervention group since the participants in the latter arm will not have completed the monthly group meetings, which extend to 11 months.

We will also conduct subgroup analyses to examine differential effects of the intervention by sexual identity (gay men vs. transgender women).

The qualitative analysis of data from the formative research and process evaluation will be based on reflexive thematic analysis, grounded in a critical realist/contextualist ontology where interviewees’ experiences are understood as lived realities that are produced and exist within broader social contexts [72–74]. The transcribed material will be managed in QSR NVIVO 13. We will conduct a reflexive thematic analysis focusing on phenomenological descriptions and narrative constructions through the following steps: (1) The interviewers note their immediate impressions and responses after the interviews to increase reflexive awareness of interpersonal processes in the interview situation. (2) Researchers read the transcribed material and the interviewers’ notes to obtain a basic sense of the interviewees’ experiences and how they give meaning to the intervention and associated processes. (3) Meaning units will be coded and the codes merged into themes. The themes will then be reviewed by the research team and refined to ensure that they capture the range of perspectives represented in the data. A second researcher will independently audit the thematic structure. The final themes will be synthesized into written text.

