#### Secondary outcomes

Psychological distress will also be assessed at 7 and 18 weeks to evaluate the short and intermediate impact of the intervention (Table 2). Whereas experiences of violence (type-specific violence and severity/high-intensity violence) will be assessed at 18 weeks and at 12 months. Each type of violence will be analysed as a separate binary outcome based on whether the participants report any act within the category. Severity or high-intensity violence will be assessed using established criteria [58], which classify several physical acts, repeated less-severe acts, frequent emotional or controlling acts, multiple emotional or controlling acts occurring once or a few times, and all sexual violence as indicators of high-intensity violence.

**Table 2 Tab2:** Description of secondary outcome measures, measurement tools, scoring, and time of measurement

Outcome	Measurement tool	Description and domains	Scoring	Time points*
Psychological distress	GHQ-12	Psychological distress over the past 2 weeks (anxiety, depression, and social dysfunction symptoms)	4-point Likert; bimodal scoring (0–0–1–1); total score 0–12	7 weeks, 18 weeks
Experience of physical violence	Modified Women’s Health Questionnaire**	Slapping, pushing, hair pulling, hitting, kicking, dragging, choking/burning, or threat/use of weapon	Binary (1 = any act; 0 = none)	18 weeks, 12 months
Experience of sexual violence	Modified Women’s Health Questionnaire	Forced sex, degrading/humiliating sexual acts or sex due to fear	Binary (1 = any act; 0 = none)	18 weeks, 12 months
Experience of psychological violence	Modified Women’s Health Questionnaire	Insults, belittling, humiliation, intimidation, or threats to harm participant or someone they care about	Binary (1 = any act; 0 = none)	18 weeks, 12 months
Experience of controlling behaviours (partner or family)	Modified Women’s Health Questionnaire	Restricting the participant’s social contact, surveillance, jealousy, restricting healthcare access, or blocking income-generating activities	Binary (1 = any act; 0 = none)	18 weeks, 12 months

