### Sample size

The SAATHI trial will enrol at least 960 participants (320 per arm). This sample size is estimated to provide 90% power to detect a standardized mean difference of 0.27 in psychological distress between the EUC arm and the SAATHI-I arm and between the SAATHI-I arm and the SAATHI-IG arm at 12 months after enrolment. Other parameters used in the sample size calculation include a standard deviation of 2.6 units [66], a two-sided α of 0.05, and a maximum assumed attrition rate of 10%. This standardized effect corresponds to an absolute mean difference of approximately 0.7 points on the GHQ-12 bimodal scale. The assumed effect size is conservative and is consistent with the range of effects reported in previous evaluations of PM + [67, 68] and with methodological work on clinically relevant effect size for psychotherapy [69].

This sample size is also sufficient to detect a 25% reduction in the proportion of participants reporting exposure to violence after receiving the PM + counselling (from 60% in the control arm to 45% in the SAATHI-I arm) at 12 months, with at least 90% power. To ensure adequate power for the planned secondary outcomes, the final planned enrolment was increased to at least 354 participants per arm (total *N* = 1062).

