There is a potential risk of contamination between study arms due to highly networked nature of the study population. Participants in the intervention arm may share information, skills, or coping strategies with peers who are enrolled in the control arm. We will attempt to minimize this risk through clear messaging during enrolment and by reinforcing the importance of not sharing intervention materials; however, some level of contamination remains possible in community-based trials. Participants in the control arm may also seek counselling or other psychosocial support services outside the study. Participants in the EUC arm will be interviewed after their final follow-up assessment and asked whether they became aware of any strategies used in the SAATHI intervention, how they received this information and from whom. These data will allow us to assess the extent and potential impact of contamination between study arms. Another risk is differential attrition. Participants in the control arm may feel they are not receiving direct therapeutic benefit and may therefore be more likely to drop out. We will document reasons for attrition where possible to help interpret results.

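### The primary analysis is complete-case under an intention-to-treat label, although the protocol names higher control-arm dropout as a risk; if dropout also relates to outcome, both 12-month estimates can be biased.

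*Protocol article*

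**What the plan says.** The Data analysis section of the protocol article sets the principle: "The quantitative analysis of effectiveness will be based on intention-to-treat with pairwise comparisons of the three arms". On missing data it then says "Primary analyses will be based on complete case analysis" and, as a robustness check, "we will perform sensitivity analysis using inverse probability weighting".

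The Discussion returns to attrition: "Another risk is differential attrition". It gives the arm and the reason: "Participants in the control arm may feel they are not receiving direct therapeutic benefit and may therefore be more likely to drop out". The response offered there is "We will document reasons for attrition where possible to help interpret results". The Data collection methods section lists retention measures: alternative contacts, reminders, rescheduling and incentives.

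Both primary outcomes, GHQ-12 and any violence, are taken at 12 months. Interim data exist for people who leave later. On GHQ-12, Secondary outcomes says "Psychological distress will also be assessed at 7 and 18 weeks to evaluate the short and intermediate impact of the intervention". Table 2 has each type of violence at 18 weeks. The Sample size section assumes "a two-sided α of 0.05, and a maximum assumed attrition rate of 10"%, without a split by arm.

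**The concern.** Anyone without a 12-month interview falls out of both primary comparisons, so the estimate describes completers, not everyone randomised. Analysing completers in their allocated arm is compatible with one use of the term intention-to-treat. It does not keep the protection of randomisation when the reason for leaving is tied to the outcome.

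The protocol's own reason for control-arm dropout is a feeling of receiving no benefit. A person who feels that way may differ in distress, or in exposure to violence, from one who stays. The 10% attrition allowance protects power but does nothing about bias. The complete-case step also takes nothing from the 7-week and 18-week values of people who later leave, although those values are the best available guide to where they were heading.

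**Working it through.** **1. The plan's own figure.** Inputs from Sample size: standardised difference 0.27, two-sided alpha 0.05, power 90%, attrition 10%.

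- n per arm = 2 × (1.960 + 1.282)² / 0.27² = 288.3, so 289.
- Allowing for attrition: 289 / 0.90 = 321.1, so 322, against the stated 320. With 320 × 0.90 = 288 completers, power is 90%.

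The sample size therefore reproduces, and the point is not an arithmetic error in it.

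**2. Bias formula.** In one arm let d be the dropout proportion and g the mean of dropouts minus the mean of completers.

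- All-randomised mean = completer mean + d × g.
- Bias of the complete-case difference (SAATHI-I minus EUC) = d_EUC × g_EUC − d_SAATHI × g_SAATHI.

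Lower scores are better, so a positive value understates benefit. If g = 0 in both arms the bias is zero however unequal the dropout. If d and g are both equal across arms the bias cancels.

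**3. GHQ-12.** The protocol gives neither d by arm nor g, so both are assumptions. The gap is taken as the same in both arms.

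| EUC dropout | SAATHI-I dropout | g (points) | Bias (points) | Share of 0.7 |
|---|---|---|---|---|
| 10% | 10% | any | 0 | 0% |
| 10% | 5% | 1.0 to 2.0 | 0.05 to 0.10 | 7% to 14% |
| 15% | 5% | 1.0 to 2.0 | 0.10 to 0.20 | 14% to 29% |

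If dropouts are better off than completers by the same amounts, the signs reverse and benefit is overstated. Equal dropout is no guarantee either: at 10% in each arm, with gaps of 0.5 SD (1.3 points) in opposite directions, the bias is 0.10 × 1.3 + 0.10 × 1.3 = 0.26 points, in either direction.

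**4. Scale.** With SD 2.6 and 354 × 0.90 ≈ 318 completers per arm, the standard error of the difference is 2.6 × √(2/318) = 0.206. A bias of 0.10 to 0.20 is 0.49 to 0.97 standard errors. With no true effect, it would raise the two-sided type I error from 5% to about 8% and 16%.

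**5. Any violence.** Take the planning values of 60% and 45% as the all-randomised truth. Assume 15% v 5% dropout, with dropouts 10 to 30 percentage points more exposed than completers in both arms.

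- Gap 10 points: completers show 60 − 1.5 = 58.5% and 45 − 0.5 = 44.5%, a difference of 14.0 points.
- Gap 30 points: completers show 60 − 4.5 = 55.5% and 45 − 1.5 = 43.5%, a difference of 12.0 points.

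The shift is 1 to 3 points against a 15-point target. The standard error is √(0.60 × 0.40/318 + 0.45 × 0.55/318) = 3.9 points.

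**The case against.** The case on the other side has real force in five places.

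- **The link to outcome is not in the text.** The Discussion speaks of a risk and of what control participants may do. It ties leaving to arm and says nothing of the later distress or violence of those who leave. A reader might infer that the protocol predicts outcome-related dropout; it does not. That step is a plausible inference from the stated reason, and no more.
- **The sizes are assumed and modest.** Read per arm, the 10% maximum excludes 15% in the control arm, and no section supports a gap of 1 to 2 points. At 10% v 5% the bias halves. In the 15% v 5% scenarios with equal gaps it stays under one standard error, and with worse-off dropouts it works against the intervention.
- **The full plan is not shown.** Data Availability mentions an analysis plan. A reader might infer that nothing anywhere tests for dropout depending on unseen outcomes, or that the interim data are never used for dropouts. A condensed article cannot establish either: a missing-not-at-random analysis and the weighting variables may be in that plan.
- **The alternative shares an assumption.** A repeated-measures model and multiple imputation rely on missingness being explained by observed data, just as inverse probability weighting does. Only a delta-shift analysis goes beyond that.
- **The label is defensible.** Intention-to-treat can mean analysis by allocated arm, so that mismatch could be cured by wording.

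All five stand as limits on strength. They do not remove the core. Complete-case analysis is a choice this article states, not a detail left elsewhere. For GHQ-12 it also rests on a stronger assumption than a model that conditions on the values already collected.

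**Conclusion.** The concern holds in a conditional form. A complete-case primary analysis under an intention-to-treat label leaves both 12-month estimates open to bias if dropout relates to outcome. The protocol itself names the arm imbalance that would let such a relation matter.

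Under the assumed 15% v 5% dropout and gaps of 1.0 to 2.0 points in both arms, the GHQ-12 bias is 0.10 to 0.20 points, or 14% to 29% of the target. It is zero when rates and gaps match, or when dropout is unrelated to outcome. The direction is unknown: worse-off control dropouts would understate benefit, and better-off ones would overstate it. The documents do not support saying that the estimate will be biased, or which way. This is a should-fix point, because the better analysis uses data already being collected.

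**What to change.** - **GHQ-12:** make the primary analysis a likelihood-based repeated-measures model with baseline, 7-week, 18-week and 12-month values all in the outcome vector, so that every randomised participant contributes. Keep the three arms separate and read the arm contrasts at 12 months.
- **Any violence at 12 months:** use multiple imputation by arm. Predictors are baseline violence, 18-week violence derived from the type-specific items, and GHQ-12 at all visits. Any violence in the previous 12 months is an entry criterion and so does not vary; the baseline predictor should be a measure that does, such as type or severity where recorded.
- **Assumption and sensitivity analyses:** state the missing-at-random assumption. Keep complete-case and inverse probability weighting as sensitivity analyses. Add an arm-specific delta-shift (tipping-point) analysis, unless the analysis plan already has one, because the new primary models do not themselves address missing-not-at-random dropout.

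The cost is some programming and revised analysis text, with no new data. If it counts as an important modification, the Ethics section requires submission to both ethics bodies before implementation. Final follow-up is due by January 2027 and no interim outcome analysis is planned, so the change can be fixed before outcomes are analysed. Made later, it would look data-driven.

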### Monitoring

The SAATHI trial has established two independent oversight committees: a Data Safety Monitoring Board (DSMB) and Steering Committee. The members of both bodies are independent of the trial’s sponsor and funder and include academic and professional experts in relevant fields such as public health, violence prevention, mental health, and biostatistics.

The DSMB holds several key responsibilities, which are to protect participant safety, monitor study progress, review adverse events, and ensure data integrity. This board will determine whether the SAATHI trial is being conducted safely. The group will conduct safety reviews in closed sessions. Following these reviews, the DSMB will communicate its recommendations to the principal investigator and the Steering Committee. No interim analysis of the outcomes data is planned; a final analysis will occur after the last participant has completed follow-up.

Meanwhile, the Steering Committee is responsible for ensuring adherence to good clinical practice and monitoring ethical compliance. Another of its core duties is to review and provide feedback on key study documents. The Steering Committee will meet at least twice a year. Together, these two committees will provide coordinated oversight of the trial’s conduct, data quality, participant safety, and scientific integrity through joint meetings and exchange of reports.

### Ethics

Prior to the commencement of the study, ethical approval was obtained from the Nepal Health Research Council (NHRC) and the Regional Ethics Committee of Western Norway (REK). Peer advocates and field researchers were oriented about ethical considerations such as sensitive behaviour when approaching participants, creating a comfortable and friendly environment, and maintaining confidentiality and privacy. Field researchers will obtain written informed consent from all participants prior to study participation. Participants with no formal education will be provided with the option of witnessed written consent. Considering the vulnerable and marginalized position of LGBTIQA +, we will ensure that participation in the trial will not lead to anyone’s sexual identity being revealed against their own will. We will ask the participants at all follow-up assessments about any adverse experiences they have had in relation to their participation in the study in order to introduce counter-measures as soon as we can. The close collaboration with the community-led organizations is also likely to help us avoid any unintended negative effects. Any important protocol modifications will be submitted for approval to the NHRC and REK prior to implementation.

If the intervention is found to be effective in the intervention arms, the study team will work with the community-led organizations and trained peers to deliver intervention sessions to all the participants in the EUC. Additional funding will be sought to support the trained peer advocates in providing assistance to all eligible and interested LGBTIQA + individuals for a defined period.

The project will be managed according to the Montreal Statement on Research Integrity in Cross-Boundary Research Collaboration.

### Dissemination plan

The study findings will be disseminated among community-led organizations, healthcare professionals, program implementers, policy-makers, and other key stakeholders in Nepal via plain-language summaries, press releases, meetings, and policy briefs to inform advocacy, guidelines, and policy-making. Furthermore, the findings will be disseminated via scientific publications in high-impact international peer-reviewed journals and conference presentations for a global scientific audience.

## Discussion

This study will be the first study to adapt the PM + intervention to LGBTIQA + populations in a LMIC and to assess the feasibility and effectiveness of engaging peer counsellors in delivering enhanced SAATHI intervention to address mental health problems in this group. The evidence obtained from the trial is likely to also be highly relevant for LGBTIQA + in other settings where the exposure to violence is high. The SAATHI intervention will target both the causes and consequences of mental health problems among LGBTIQA +.

The use of peers as counsellors appears to be a promising, innovative, and cost-effective intervention to support LGBTIQA + individuals who are afraid to disclose about their identity. Studies on the involvement of peers in addressing mental health issues among LGBTIQA + have not been conducted in LMICs. The study findings might bridge the gap in mental health service providers for LGBTIQA +, not only in Nepal but in other LMICs too. The study will also aid in building the capacity of the community-led user organizations that will be involved during the preparatory and implementation phases of the study and the final dissemination of study findings. This will ensure that the interventions will be relevant for their needs and also minimize the risk of any unintentional harm. In addition, the intervention is expected to foster capacity building and empowerment within the LGBTIQA + community by training peer advocates who can continue to support community members beyond study period. We do not expect scalability to be a problem although resources in most LMICs are limited because this will be a low-cost intervention that can be implemented by the LGBTIQA + community itself.

We have identified and considered several potential barriers to the successful adaptation and implementation of the intervention. Addressing mental health disparities requires a focus on populations who are hard to reach within and outside formal health care systems. We anticipate that recruitment of transgender women may be more straightforward, whereas lesbians and gay men may be more difficult to identify and enrol. However, considering that we will recruit participants through user organizations, we assume that other groups than transgender women will also come forward.

There is a potential risk of contamination between study arms due to highly networked nature of the study population. Participants in the intervention arm may share information, skills, or coping strategies with peers who are enrolled in the control arm. We will attempt to minimize this risk through clear messaging during enrolment and by reinforcing the importance of not sharing intervention materials; however, some level of contamination remains possible in community-based trials. Participants in the control arm may also seek counselling or other psychosocial support services outside the study. Participants in the EUC arm will be interviewed after their final follow-up assessment and asked whether they became aware of any strategies used in the SAATHI intervention, how they received this information and from whom. These data will allow us to assess the extent and potential impact of contamination between study arms. Another risk is differential attrition. Participants in the control arm may feel they are not receiving direct therapeutic benefit and may therefore be more likely to drop out. We will document reasons for attrition where possible to help interpret results.

### Trial status

Recruitment started in May 2025. As of 29 December 2025, 1054 participants have been enrolled. Participant recruitment is expected to be completed by early January 2026, and final follow-up will be completed by January 2027.

## Data Availability

Collaborators and qualified independent researchers may request access to the de-identified individual participant data and supporting documentation (e.g., codebooks and analysis plan) by submitting a reasonable written request to the principal investigator (PI). Contact information will be provided in the scientific publications associated with the study. To protect participants’ privacy, a de-identified dataset will be shared only after the publication of findings related to primary and secondary outcomes. The shared dataset will exclude identifying variables such as age, study district, and gender identity.

